### 7a. Procedures—prospective (post) group

#### *7a i. Identification of potential subjects and informed consent*

The study will enroll HIV-positive pregnant women not yet on ART. At the study site, the site's staff will inform such women about the study immediately after routine post-test counseling or, for patients already known to be HIV-positive, at their first antenatal visit. The site staff will explain that a study is underway and ask if the patient wishes to learn more about it. Patients who indicate that they may be interested in participating in the study will be referred to a study assistant. Those who do not wish to participate will proceed with a standard clinic visit.

Site counselors who perform the pre-screening will record in a notebook patients whom they do not refer for screening, to allow the study to collect aggregate statistics about the overall patient population and compare it to the screened population. Fields that will be recorded in this notebook are date, age in years, gestational age in weeks, and primary reason for not being screened. (We anticipate three main reasons: patient's emotional condition; patient's physical condition; refusal. An "other" field will allow the counselor to record any other reason.) No identifiers of any kind will be collected in this notebook, which is intended to provide only aggregate information.

Upon referral to the study assistant, patients will receive a more complete description of the study, including why it is being done, the steps involved, and the need for written informed consent. They will be assured that participation is voluntary and that they can withdraw from the study at any time, without affecting the quality of care provided by the site. They will also be offered the opportunity to ask questions. They will then be asked to provide written informed consent to participate.

The study assistant will complete a short screening form to record details about each patient screened. The screening form will not collect any identifiable information pertaining to individual patients prior to receipt of written informed consent.

#### *7a ii. Questionnaire*

After a subject consents to be in the study, the study assistant will administer the same questionnaire as used in Track 1, documenting the subject's basic demographic and socioeconomic characteristics, primary reason for seeking an HIV test or HIV care, and costs incurred per clinic visit. Height and weight will be recorded to help assess balance between the two study groups (pre and post). Additional questions will be added to the questionnaire to record basic information about the current pregnancy, including estimated gestational age, previous exposure to antiretroviral drugs for PMTCT, and number of other children.

Following administration of the questionnaire, study subjects will be thanked and escorted back to the clinic's ANC staff to continue a routine antenatal visit.

#### 7b. Procedures—retrospective (pre) group

Subjects for the Track 2 “pre” group (pregnant women offered standard care by the site before the guideline change) will be selected from the site's PMTCT register. Subjects who meet inclusion/exclusion criteria will be enrolled consecutively up to the maximum sample size for this component of the study is reached. Data collection for these subjects will be by record review only.

#### 7c. Follow up

Direct study interaction with Track 2 study subjects will cease as follows:

- *Prospective (post) group*: after administration of the questionnaire, at which point subjects will be managed by the study site following standard procedures.
- *Retrospective (pre) group*: no direct interaction at any time during the study.

#### 7d. Record review

Study subjects will be followed through review of routine medical records kept by the study site for a minimum of the remaining months of pregnancy prior to delivery. Subjects will continue to be followed in the medical records after delivery until the final date of study data censoring, up to a maximum of 24 months after study enrollment.

Delivery information (date and outcome of delivery) that is not found in the study site's own records will be sought at one of the maternity ward facilities to which women are regularly referred for delivery, Tembisa Hospital and Esangweni Clinic. A letter indicating the approval of these facilities for this limited data collection will be submitted to the IRB prior to data collection. At these facilities, the delivery ward register and/or patient files will be used to fill in missing fields in study subject records. No additional data fields beyond what are already included in the consent forms and CRFs will be collected from these facilities. This procedure is necessary to address the problem of information that is supposed to be recorded in the study clinic files but is missing due to incomplete communications between the study clinic and delivery facilities.

### **8. Data Collection and Management**

#### 8a. Sources of data

The study will collect data from four sources, as follows:

1. Screening form. Screening forms will be completed to confirm study eligibility and consent.
2. Case report form. The study nurse will use the CRF to record all steps taken by the patient and provider during the period of study interaction. The CRF will include a short questionnaire to be administered to all subjects upon consent.

3. Medical records. Routinely collected medical record data will be abstracted from medical records maintained by the study site in electronic and paper format.
4. Pre-screening notebook. Aggregate statistics about the number of potentially eligible patients not screened for the study and the reasons for not screening will be calculated from notebooks used by clinic counselors.

#### 8b. Screening form and pre-screening notebook

The study assistant will complete a screening form for each patient referred after pre-screening. The screening form will record whether the patient meets each inclusion and exclusion criterion, provides written informed consent, is eligible for ART, and is eligible for study enrollment. For patients enrolled, the Study ID number and medical record number will be added to the screening form, which will become part of the case report form for study subjects. Track 1 and Track 2 will have different screening forms.

Study counselors will enter a row in a pre-screening notebook for patients not referred for screening. This will allow aggregate information about the overall patient population to be collected and help determine whether those who were not screened differed from those screened. Data will be on sex, age in years, and reasons for not being screened. No identifiers will be recorded or collected.

#### 8c. Case report form

The study nurse will be responsible for completing a case report form for each study subject. The CRF will record consent, meeting of inclusion and exclusion criteria, enrollment, study group, and study identification number for all subjects. For Track 1, it will also record completion and results of lab tests, physical exam, and educational/counseling session; the decision to dispense ARVs; and any other information pertinent to the subject's participation in the study. This form will also record the dates and times (hour: minute format) at which each subject enrolled in the study, completed intermediate steps, and was dispensed ARVs. The CRF is expected to be completed (fully filled out) by the end of the day on which the subject is initiated on ART.

For those offered standard initiation, the CRF will record treatment eligibility when that information becomes available (usually upon receipt of CD4 count results from the off-site laboratory). No further information will be entered into the CRF for these subjects, as follow-up from this point on will be by record review only.

The CRF will include a short, closed-ended questionnaire to be administered in both tracks by the study assistant after consent. The questionnaire will elicit basic information about:

- Demographic characteristics of patient and patient's household (marital status, household composition, duration living in current location)
- Socioeconomic characteristics of patient (employment status, income level)
- Costs to patient of obtaining care at site (transport costs, loss of income, etc.)
- Primary reason for seeking an HIV test (symptoms, pregnant, partner diagnosed, concern about personal risk, etc.), history of previous HIV tests, household members with HIV/on ART, previous use of the study clinic

The last page of the CRF will include identifying information about the subject, including name, date of birth, and national identification number. This information will not be entered into the study database but will be used only for matching CRF and medical record data. This information will be collected for both study tracks (in Track 2, prospective group only), as matching CRF data to medical record data will be necessary for both tracks.

Only some components of the CRF will be used for subjects in Track 2 (questionnaire, receipt form, identification form), not the entire form.

#### 8e. Medical record data

Most data for the study will be collected from the site's routinely maintained electronic medical records, which are maintained in an information system called Therapy Edge-HIV™. Records in this information system are typically only created once a patient starts ART. Paper-based medical records kept by the site will therefore be used to supplement the electronic medical record system as needed. The fields to be collected are listed below.

*To be used to link electronic and paper-based records to study identification number only:*

- Electronic medical record system number
- Clinic file numbers
- National ID number
- Name
- Date of birth

*All subjects at baseline (ART initiation):*

- Date of positive HIV test (if available)
- Sex
- Age in years
- Weight and height or BMI
- Date treatment eligibility determined, if reported
- Date and result of eligibility-determining CD4 count
- Date and result of TB symptom screen
- Date, type, and result of TB test(s)
- TB treatment, if relevant
- WHO stage and clinical conditions
- Date ART initiated (first dose of drugs dispensed)
- First-line regimen prescribed

*For all clinic visits for duration of study follow up, including initial visit and pre-ART visits (to be used to estimate resource utilization):*

- Date of visit
- Primary reason for visit (e.g. scheduled medical visit, medication pickup, unscheduled medical visit)
- Types of professionals seen (e.g. nurse, doctor, pharmacy assistant, counselor)
- Group and individual sessions attended (e.g. wellness course, adherence education)
- Numbers and types of all lab tests conducted (including CD4 counts and viral loads)
- Other procedures (e.g. x-rays) performed

- Medications prescribed and dispensed (ARV and non-ARV)
- Admissions for inpatient care since previous visit, if recorded
- Details of inpatient care received (facility, number of days, medications, lab tests, etc.) if recorded

*At interim and final dates of data censoring:*

- Date and result of most recent viral load test
- Status at clinic (in care / died / transferred to another site / stopped care / lost to follow up, defined as > 1 month late for last medication pickup)
- New or recurring HIV-related conditions
- Date and cause of death if applicable
- Date and result of most recent CD4 count

*Track 2 subjects only (pregnant women):*

- Gestational age at diagnosis or first ANC visit for current pregnancy if previously diagnosed
- Prior exposure to PMTCT
- Date of delivery
- Medication pickup dates and quantities of ARVs dispensed
- Number of weeks on ART at delivery

Paper-based medical records maintained by the study site will be accessed when necessary to confirm or supplement information in the electronic medical record system. Paper records and registers will be used for subjects in the retrospective group of Track 2, who will initially be selected from the PMTCT register, and for the retrospective comparison group of Track 1, who will initially be selected from the HCT register. Paper files and clinic registers will also be used if it is found that routine data entry into the electronic medical record system is incomplete or backlogged. Paper medical records or records kept in a different electronic medical record system will also be used for patients who transfer to another clinic during the study follow up period and consent to have their new clinic's records accessed.

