##### *6c i. Rapid CD4 count and TB symptom screen*

The first step for rapid initiation will be a venous blood draw for a rapid CD4 count (and for other treatment initiation tests for those found eligible for treatment). For those offered rapid initiation, the blood sample will be processed immediately, on site, using the Pima Analyzer, rather than being stored for later transport to an off-site laboratory. The processing time for the Pima test is 20 minutes. In a validation study of Pima used at point of care clinics in South Africa, 7-9% of tests could not be read or had invalid results, due primarily to user errors in obtaining blood samples or filling cartridges. Careful training will be provided to study staff to minimize this type of error. A second Pima test will be run for subjects for whom the first Pima result is invalid. In addition, a blood sample will be sent to the off-site National Health Laboratory Service (NHLS) laboratory for all subjects in the rapid group for a confirmatory CD4 count. NHLS lab results will be monitored by the study team, and any subject found

not eligible for treatment using Pima but eligible based on lab results will be contacted by the study assistant and asked to return to the clinic to initiate treatment following rapid initiation procedures.

Patients who already have with them a valid CD4 count result (sample taken within the previous 6 months) will not have an additional CD4 count, though a blood sample will still be drawn for other required laboratory tests.

While awaiting CD4 test results, the study nurse will administer a TB symptom screen following South African guidelines for the definition of symptoms, for all subjects not already on TB treatment. Subjects with any TB symptoms will be asked to provide a sputum sample. The study nurse will also ask the subject about symptoms that might indicate a Stage 4/3 condition. Subjects who report such symptoms will be given a physical examination to determine if the condition exists and what treatment is needed.

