#### *6d i. Determination of treatment eligibility*

Following the study site's usual procedures, subjects in the standard group will be asked to give a blood sample for a CD4 count on the day they test positive for HIV. Samples are sent to an off-site laboratory for processing, with results typically available in approximately one week. Patients are then asked to schedule a return visit one week later to receive their CD4 count results and be informed of their eligibility for ART.

For study subjects receiving standard care, with whom the study team will have no direct contact after study enrollment, laboratory results will be monitored to determine those who are treatment-eligible and should be enrolled in the study. No further data will be collected for subjects who are not eligible for treatment. Follow up of those who are eligible for treatment will be by passive record review only, as described below.

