Variables considered to be important in the univariate stage will be included in multivariate models. Adjusted analyses will include covariates which are unevenly distributed across groups and which could plausibly affect viral suppression or time to ART initiation. These potential confounders include demographic (e.g. age, sex) and socioeconomic (education, distance from clinic, employment, etc.) variables, medications, baseline CD4 counts, prior receipt of PMTCT, and low BMI, among others. Each of these models can then be used to look for patient-level predictors of treatment uptake, viral suppression, and retention in care.

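### The one baseline CD4 result listed for abstraction names no assay, and for Track 1 subjects newly tested at enrollment the assay mostly follows the randomized arm

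*Protocol*

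**What the plan says.** **Field collected.** The baseline list in Protocol 8e has a single CD4 item: "Date and result of eligibility-determining CD4 count". It has no entry for the type of test, although the TB test item in the same list asks for type. The per-visit list in 8e takes the numbers and types of laboratory tests, not their results. A further CD4 result is taken at data censoring, but it is the most recent one.

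**Rapid arm.** Section 6c i says "the blood sample will be processed immediately, on site, using the Pima Analyzer", and 6b vi and 6c i tell subjects whether they are eligible as soon as that result is ready. In addition, "a blood sample will be sent to the off-site National Health Laboratory Service (NHLS) laboratory for all subjects in the rapid group" as a confirmatory count, and the study team monitors those results.

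**Standard arm.** Section 6d i: "Samples are sent to an off-site laboratory for processing, with results typically available in approximately one week". Section 8c has the CRF record eligibility for this arm when the off-site result arrives.

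**Exceptions.** Under 6b i, subjects may be recruited when they collect a CD4 result of 350 or below. Under 6c i, rapid subjects who carry a valid count from the previous six months have no new one, and those found "not eligible for treatment using Pima but eligible based on lab results" are called back.

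**Use.** Section 11b begins with a comparison of baseline predictors and then gives crude risk ratios. Its adjustment rule is: "Adjusted analyses will include covariates which are unevenly distributed across groups and which could plausibly affect viral suppression or time to ART initiation". Baseline CD4 is a named candidate, and the same models serve to look for predictors.

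**The concern.** Among subjects tested at enrollment, randomization decides which instrument fills the baseline CD4 field. If Pima reads systematically lower or higher than the laboratory, the baseline table shows a CD4 difference that is partly an instrument difference. Section 11b admits covariates because they look uneven, so that difference can itself bring CD4 into the model. The adjusted risk ratio is then moved by an artifact. The predictor analyses also pool two measurement scales.

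At stake are the credibility of the baseline table and of the adjusted and predictor analyses. The crude primary comparison is not at stake.

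**Working it through.** The plan states no figure on this point, so there is none to reproduce. The check traces the source of the field and then sizes the effect.

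**Step 1: source of the field in Track 1**

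| Route | Rapid arm | Standard arm |
|---|---|---|
| Newly tested at enrollment | Pima (6c i) | Off-site laboratory (6d i) |
| Pima above threshold, NHLS eligible | NHLS laboratory (6c i) | Not applicable |
| Valid or returned earlier count | Earlier count, assay not stated (6b i, 6c i) | Earlier count, assay not stated (6b i) |

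The first row separates the arms by assay. The second and third rows dilute the contrast. In simulation the NHLS-only route supplies about 0.5% to 8% of rapid-arm CD4 eligibility. The protocol does not give the share with an earlier count.

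**Step 2: inputs**
- 200 per arm: enrollment of 400 at 1:1 (section 10).
- 70% eligible (section 10), applied as 70% of counts at or below 350.
- Assumed, not in the protocol: square-root-normal CD4; SD among the eligible about 95; CV 6% laboratory and 12% Pima; Pima bias of -10 to -40 cells; log risk ratio of 0.05 to 0.20 per 100 cells.
- Rapid subjects enter if either assay is at or below 350; standard subjects enter on one laboratory count.

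**Step 3: difference in the recorded field**

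Selection acts on the measured value. A low-reading Pima also admits people whose true counts are higher, so the recorded difference is smaller than the bias.

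Hand check: SE = 95 x sqrt(2/200) = 9.5. With d the difference in recorded means, the chance of |z|>1.96 is Phi(|d|/9.5 - 1.96) + Phi(-|d|/9.5 - 1.96).

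| Assumed bias | Recorded difference | abs(d)/9.5 | Hand check | Simulations |
|---|---|---|---|---|
| -10 | about -3 | 0.32 | 6% | 6-7% |
| -20 | about -10 | 1.05 | 18% | 17-21% |
| -30 | about -17 | 1.79 | 43% | 41-46% |
| -40 | about -24 | 2.53 | 71% | 65-75% |

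The lower ends come from a run in which the rapid-arm SD was about 103. At -40 its difference was about -23 and its SE sqrt(95^2/200 + 103^2/200) = 9.9, so z = 2.3 and the chance is about 64%.

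The sign of the bias is also unknown: an assumed +20 gives about +20 cells. If 30% of rapid subjects bring an earlier laboratory count, the figures for -20, -30 and -40 fall to about 11-13%, 23-27% and 39-47%. If half do, they are about 8%, 15% and 25%.

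**Step 4: effect on the adjusted risk ratio**

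Shift from the crude value = exp(slope x difference/100). At the extreme, exp(0.20 x 24/100) = 1.049, about 5%. At the smallest slope and difference, exp(0.05 x 3/100) = 1.002.

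**Step 5: what a common assay leaves**

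With laboratory counts in both arms, a difference of about +4 to +20 cells remains across the assumptions tried, because rapid subjects can qualify on either assay. At a bias of -40 the laboratory difference is about +19 while the recorded field shows about -24. The field can therefore have the wrong sign.

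**The case against.** The strongest reply is that choosing which of two available counts is baseline is a variable definition, commonly left to an analysis plan that is not at hand. A laboratory count is planned for both arms, the team monitors the NHLS results, and 8c says the Track 1 CRF records laboratory results. Section 11b does not say that its baseline CD4 is the 8e field.

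Part of this stands: nothing compels the analyst to use Pima. But the eligibility-determining count is the only baseline CD4 result on the abstraction list. The CRF is expected to be complete by the day of ART initiation, when an off-site result may still be pending. An analysis plan can use the laboratory value only if it was captured and labeled.

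Three stronger readings are tempting and are not supported:
- **That the rapid-arm value is always Pima.** Sections 6b i and 6c i provide for earlier and NHLS-only counts.
- **That the full assay bias passes into the field**, so that imbalance is flagged in up to 99% of trials and the risk ratio moves by 8%. This ignores that rapid subjects are selected on the measured count.
- **That the primary result is compromised.** The crude risk ratio in 11b and the unadjusted interim test in 12g do not use CD4.

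It is also fair that 11b sets no significance threshold for unevenness; p<0.05 here is illustrative only.

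**Conclusion.** The point holds in limited form. As listed, the baseline CD4 field mostly follows the randomized arm's assay for subjects newly tested at enrollment, with no record of which assay was used. The baseline comparison, adjusted risk ratios and predictor models that draw on it partly compare instruments.

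The size cannot be fixed from the protocol, which gives Pima's unreadable or invalid rate (7-9%) but no agreement with the laboratory. The effect is negligible at a bias of -10 cells and substantial for the baseline table at -30 to -40. For the adjusted risk ratio it is small throughout. All of this assumes that most rapid subjects have a Pima count and that eligibility is by CD4.

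A reader might infer that a common assay would restore balance. It would not: entry on either assay makes the rapid arm's composition differ in fact, and that is a separate matter.

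**What to change.** - In 8e and 11b, define baseline CD4 in both arms as the off-site laboratory (NHLS) count closest to randomization and drawn before ART initiation. The pre-ART limit is needed so that a later count is not taken as baseline for a subject with no new count at enrollment.
- Use that value in the baseline table, adjusted models and predictor analyses.
- Record assay and date for every CD4 count, including earlier counts that subjects bring, and keep the Pima result as a separate field.
- Confirm that the off-site laboratory in 6d i is the NHLS laboratory named in 6c i; the protocol does not say so.
- Reconcile two statements in 6c i: a sample goes to the NHLS "laboratory for all subjects in the rapid group for a confirmatory CD4 count", yet those with a valid earlier result have no further count.

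The cost is one abstracted field from results the team already monitors, a sentence or two of wording, and possibly a few missing laboratory values. It adds no patient burden and does not change the sample size.
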